## Background

Sepsis is a life-threatening acute organ dysfunction secondary to infection [1]. Acute care hospitals in the United States (US) discharge over 1.5 million sepsis survivors annually [1–4]. Across diverse healthcare systems, 30-day hospital readmission rates are consistently high for survivors [5–9]. Sepsis is a serious illness and survivors are vulnerable to substantial post-discharge morbidity and mortality [10], with readmission rates rivaling those for heart failure, pneumonia, and myocardial infarction [5, 11, 12]. Annual health care costs for sepsis survivors are nearly double the costs of these other conditions [12]. Sepsis survivors are twice as likely as non-sepsis patients to be readmitted by 30 days [12], often with a new or recurrent infection [13] with 32% of these 30-day readmissions occurring within 7 days [6, 14], and in-patient costs alone ranging $23.7 [15] to $27 billion per year [16] making sepsis the costliest inpatient diagnosis in the US [17]. When hospitalized, these vulnerable, mainly older adults, are exposed to increased risk for hospital-acquired infections and medical errors [18]. Sepsis survivors often experience impaired functional status [19], reduced quality of life [20], and accelerated cognitive decline [20], all of which are associated with a shortened life span [21]. A subset of sepsis survivors, especially those who experience these complex sequelae, may greatly benefit from goals of care discussions and palliative care [22, 23].

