The first homecare visit, usually conducted by a registered nurse, is one of the most critical steps of the home care episode [35, 36], and is important for continuity of care [18, 37, 38]. Too often the HHC nurse conducts the admission visit with fragmented, incomplete, or inaccurate knowledge of the patient’s clinical condition [39, 40]. In our prior work, among sepsis survivors readmitted by 30-days, 33% of hospital readmissions occurred within 7 days. Moreover, we found a mismatch between the hospital diagnoses and the HHC diagnoses, indicating HHC clinicians may not know the patient is a sepsis survivor [14]. For hundreds of thousands of sepsis survivors, the most frequent diagnoses in HHC were pneumonia and urinary tract infection, with sepsis ICD codes appearing only 4% of the time [14]. Further, most of the 7-day readmission risk factors identified by our team were noted after the HHC admission [14]. It is too late to wait for the HHC assessment to occur on the first home visit (which could occur several days after hospital discharge and be available to others in the record up to 5 days later). Providing high quality information from the acute care referral source to increase awareness of the sepsis survivors facilitates accurate care planning and supports provision of earlier visits, higher quality care, and prevention of avoidable, early rehospitalization for a sizable and increasing population of sepsis survivors [41–44]. The National Consensus Project Clinical Practice Guidelines for Quality Palliative Care support access to palliative care throughout the trajectory of severe illnesses like sepsis, increasingly in community or home settings. Improving the transfer of information can increase access to these resources, which can enable patients and families to receive support in their homes [45]. For these reasons, our intervention starts in acute care to improve identification of the sepsis survivor and to highlight the diagnosis for HHC clinicians.

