Implementation of the I-TRANSFER components will be guided by the stakeholders and research team using intervention mapping, as described below. The context and determinants (barriers, enablers), processes, and strategies encountered during Aim 1 will be collected for Aim 2 analysis. Hospital partners will work with the study and HHC team to achieve the following components of I-TRANSFER: identify the sepsis survivors during the hospitalization, make the outpatient follow-up appointment before discharge, notify the HHC agency of a sepsis survivor, conduct timely home health visits and outpatient visits in week one. Based on our preliminary work, we have identified several effective strategies that we can suggest to better identify the sepsis survivor, including generalizable use of sepsis order sets within the electronic health record [14]. We will also recommend use of the Centers for Disease Control (CDC) Epicenters Sepsis Clinical Surveillance Definition, which has the advantage of identifying confirmed cases of sepsis given the criteria of sustained antibiotic delivery [35, 77, 78]. We will examine fidelity to these recommended components as potential implementation enablers.

Challenges we expect to face in making and achieving a timely outpatient visit are limited appointment availability, and patients who cancel or do not attend the visit. A potential strategy is to increase awareness about I-TRANSFER’s evidence and include a script for the clinician to educate the patient about the value and importance of the outpatient visit. Transportation may be an issue as well and will be brainstormed for solutions with the stakeholders and tracked as a barrier. Hospital based personnel will notify the HHC intake department when the patient is a sepsis survivor. The intervention mapping will determine the workflow for this component with each site. It may include phone calls, text messaging, faxed or electronic documents.

HHC intake personnel will likely schedule the nurse visits and notify the visiting nurse of the sepsis diagnosis and date of the outpatient appointment. To meet protocol, the first registered nurse home visit will occur within 2 days of hospital discharge, with a second visit that week. The patient will be encouraged and assisted if necessary (e.g. transportation) to attend their scheduled outpatient appointment.

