### Measures and outcomes

#### Aim 1, effectiveness of the I-TRANSFER intervention

The primary outcome of Aim 1 is 30-day all-cause hospital readmissions. Secondary outcomes are number of inpatient days (if rehospitalized), and ED use within 30 days, all measured through the Medicare Administrative Data.

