In addition to the survivors from the treated dyads in the baseline period, additional control survivors will be used to provide a much larger sample of control observations. These observations will be drawn from the population of Medicare sepsis survivors not being cared for by any of the participating institutions. This sample is unlikely to be balanced on covariates, a priori, with the sample of survivors from participating providers. Therefore, entropy balancing will be used to create sampling weights for these observations to produce balance on covariates. All hierarchical regression analyses will take these entropy balance weights into account. In addition to an intent-to-treat indicator, the regression will include covariates specified by the Andersen Behavioral Model. Inpatient days after the index discharge will be modeled using hierarchical Poisson regression. ED utilization will be modeled using hierarchical logistic regression.

The pragmatic aspects of the study design make it important to conduct various sensitivity and exploratory analyses. Sensitivity analyses will include checks of robustness of findings with and without sepsis survivors who are readmitted shortly after discharge (e.g., within 7 days), those with a resumption of HHC episode, discharges with very short (1 day) or very long hospital stays (30 days or more), and survivors less than 65 years old. Exploratory analyses will include estimation stratified by type of sepsis, sex (as a biological variable), and hospital ownership status.

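### Dropping survivors readmitted within about 7 days changes the quantity estimated, so it cannot serve as a robustness check on 30-day readmission

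*Protocol article*

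**What the plan says.** In the Analysis section for Aim 1, the protocol article states: "Sensitivity analyses will include checks of robustness of findings with and without sepsis survivors who are readmitted shortly after discharge". The group left out in the second run is those "readmitted shortly after discharge (e.g., within 7 days", so the 7-day cut is given as an example. The same list contains checks on resumed home care episodes, very short or very long index stays, and patients under 65. No reason is given for the early-readmission exclusion, and nothing is said about what it estimates.

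Three other parts of the article bear on it:

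- **Outcome** (Measures and outcomes): "The primary outcome of Aim 1 is 30-day all-cause hospital readmissions". Days 0-7 lie inside that window.
- **Delivery** (Study design): partners are to "conduct timely home health visits and outpatient visits in week one", and to meet protocol "the first registered nurse home visit will occur within 2 days of hospital discharge, with a second visit that week". The Aim 2 process hypothesis places the community provider visit by day 7.
- **Event timing and purpose** (Background): one sentence has "with 32% of these 30-day readmissions occurring within 7 days"; the authors' prior work found that "33% of hospital readmissions occurred within 7 days" among survivors readmitted by 30 days. Better referral information is said to be valuable because it "supports provision of earlier visits, higher quality care, and prevention of avoidable, early rehospitalization".

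The main analysis is intent to treat (Study period) and covers all eligible hospitalizations followed by home care (Analysis).

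**The concern.** Index length of stay and age are fixed by the time of discharge, so restricting on them leaves the outcome definition alone. Early readmission is different: it happens after the intervention has started, it is part of the primary outcome, and it is among the events the intervention is meant to prevent.

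Removing these patients selects on the outcome. If the visits keep some intervention patients out of hospital in week one, those patients stay in the analysis while comparable usual-care patients are dropped. The two remaining groups then differ in composition as well as in exposure.

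What is at stake is interpretation. Under a robustness label, a smaller or reversed estimate invites doubt about the main finding, and a larger one invites false reassurance. Either can arise from effect timing alone.

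**Working it through.** **Inputs.** The usual-care 30-day rate is 23% and the target reduction 7 points (Study sample), so 16% under the intervention. The early share of readmissions is 32% or 33% (Background); 33% is used here for usual care. How the 7 points divide between week one and later is not in the article, so it is varied as an assumption.

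**The plan's own figures.** 7/23 = 30.4%, as stated. The stated 400 per interval is approached by a two-proportion formula at one-sided 5% with 80% power (396) or two-sided 5% with 70% power (395). The article gives neither error rate, and the figure does not affect this point.

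**Events removed.** Usual care, days 0-7: 0.23 × 0.33 = 7.59 points (7.36 at 32%). Days 8-30: 23 − 7.59 = 15.41 points. The exclusion deletes about as many points of usual-care events as the whole target effect.

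**Formulas.** Let E be the risk of readmission in days 0-7 and L the risk in days 8-30, so the 30-day risk is P = E + L. After exclusion the rate is L/(1 − E) and the odds are L/(1 − P). Usual care becomes 0.1541/0.9241 = 16.7%, with odds 0.1541/0.77 = 0.2001.

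| Assumed timing of effect | Intervention E, L (points) | Intervention rate after exclusion | Difference (points) | Odds ratio after exclusion |
|---|---|---|---|---|
| All after day 7 | 7.59, 8.41 | 0.0841/0.9241 = 9.1% | 7.6 | 0.500 |
| Proportional | 5.28, 10.72 | 0.1072/0.9472 = 11.3% | 5.4 | 0.638 |
| Half in week one | 4.09, 11.91 | 0.1191/0.9591 = 12.4% | 4.3 | 0.708 |
| All in week one | 0.59, 15.41 | 0.1541/0.9941 = 15.5% | 1.2 | 0.917 |
| 2 points delayed, both groups 23% at 30 days | 5.59, 17.41 | 0.1741/0.9441 = 18.4% | −1.8 (apparent harm) | 1.130 |

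Without exclusion, the first four rows all have a difference of 7.0 points and an odds ratio of (0.16/0.84)/(0.23/0.77) = 0.638; the last has a difference of 0. An early share of 32% gives the same differences to one decimal in the four 7-point rows.

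**Why the proportional row keeps its odds ratio.** If the early share s is the same in both groups, the odds after exclusion are (1 − s)P/(1 − P), and (1 − s) cancels.

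**Power.** With 869 per period, taken as the size of each group, a two-sided 5% test and no allowance for clustering or weights, power is 96% with everyone kept. After exclusion it is above 99% (all after day 7), 88% (proportional), 69% (half in week one) and 10% (all in week one). Clustering would lower each figure.

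**The case against.** Five arguments can be made for leaving the text alone.

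1. **It is one supplementary item, run with and without these patients.** The full result always stands beside it, and no rule lets a discrepancy overturn the main finding. This stands: the primary estimate is not biased. A reader might infer that the trial's main result is compromised; the intent-to-treat analysis keeps these patients, so it is not.
2. **The distortion need not go one way.** A reader might infer that the exclusion always hides a real effect. The article does not support that. It says when visits occur, not when benefit accrues, and a late benefit would look larger.
3. **On the likely model scale, a proportional effect is not attenuated.** The article plans generalized mixed models and names logistic regression for other binary outcomes. A logit model for readmission is an inference, but if it is used the fall from 7 to 5.4 points is a feature of the risk-difference scale. What is lost is events and power.
4. **The extreme row is unlikely.** All in week one requires preventing 7.0 of 7.59 points, a 92% cut, although some visits may come late in that week. The 2-point delay is an invented illustration. Both mark the range and are not forecasts.
5. **There may be a reason for the check.** The Background reports earlier uptake among survivors not readmitted in the first week. A 7-point drop described as a 41% relative reduction implies a base of 7/0.41 = 17.1%, close to the 16.7% left after exclusion. The link is an inference. In that study exposure was visits actually received, so an early readmission could stop a patient from being classed as exposed. Here exposure is an intent-to-treat indicator, and that reason does not carry over.

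The article's use of 7 days as an example does not rescue the check: any early-readmission cut-off has the same defect.

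**Conclusion.** The exclusion is not a valid check of robustness for 30-day readmission. It removes about a third of usual-care primary events, selects on something the intervention may change, and answers a different question. With the same true 7-point effect, the reported difference could lie anywhere from 1.2 to about 7.6 points, depending only on timing. With no 30-day effect at all, a 2-point delay would appear as a 1.8-point harm. Agreement or disagreement with the main result therefore says little about its robustness.

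The sizes rest on 23% against 16%, a 33% early share in usual care, and assumed effect timing; covariates, weights and clustering are ignored. This is a flaw of interpretation in a secondary analysis, worth correcting before the data are analysed.

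**What to change.** Replace the exclusion with two outcomes, first readmission in days 0-7 and first readmission in days 8-30. Each should be analysed over all index discharges with the model used for the 30-day outcome, and reported together with the 30-day result. The two unadjusted risk differences then add up to the 30-day difference. Under a proportional effect, for example, (7.59 − 5.28) + (15.41 − 10.72) = 2.31 + 4.69 = 7.00 points.

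If a day-8 landmark is wanted for comparison with the earlier study, keep it, but label it descriptive, state that it estimates days 8-30 readmission among those not readmitted by day 7, and take it out of the robustness list.

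The cost is small: claims dates already give the timing, so it is a wording change and slightly more reporting. There are two downsides. Dropping the landmark loses some direct comparability with the earlier study. The days 8-30 result also cannot be read alone: in the delay example it would show 15.4% against 17.4%, offset by 7.6% against 5.6% in days 0-7.

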#### Aim 2, I-TRANSFER implementation

The recorded needs assessments and CFIR interviews will be transcribed by a secure, professional service. All study materials will be stored in a secure, password protected site. The typed interview transcripts and observation notes will be uploaded into qualitative software NVivo 11.0 [50] to facilitate data organization, analysis across the research team, and documentation of steps in the workflow. The data analytic team will train together to complete the thematic analysis [89] of the transcripts and field notes. The team members will independently read through 4 randomly selected interviews taking notes on the substantive areas of content. Content identified by the research team members in this initial reading will be compared to each other and a provisional structure of the coding scheme, partially deduced from the CFIR domains, will be developed by the team [90]. The trained research assistants will complete the coding of the remaining data, meeting weekly with the investigators to review findings and confirm agreement. Ambiguities, incompleteness, lack of clarity, differences and commonalities will be discussed and resolved in weekly meetings. Alternative approaches in workflow, barriers, facilitators, and differences in acceptability observed between the study sites will be noted, compared, contrasted, and reported as study results so agencies with similar barriers can see suggested solutions to increase generalizability of the findings. NVivo 11.0 software can accommodate ongoing changes and additions to the labels describing the implementation determinants within each concept of the CFIR framework. Through constant comparative analysis, results will be refined for conceptual flow and consistency.

Strategies to increase and ensure the trustworthiness and scientific adequacy of the study include credibility (iteratively member checking the findings with the site implementation teams); and transferability (developing a thick description, notes and diagrams taken during the interviews and implementation mapping) [46]. Credibility relies heavily on input from the implementation teams and the national advisory group. Conference calls will share methods and findings with the groups to gain insights and reactions. Second, transferability or generalizability will be strengthened by collecting “thick” descriptive data that will permit comparisons with other contexts to which transfer might be contemplated. After the data collection is completed, the presentation of findings will contain a full description of contextual factors, determinants, process, and strategies so that the reader (future dyads) will be able to ascertain if they can apply the results to their situation. Third, dependability will be strengthened by conducting an audit that examines processes and strategies during implementation. Fourth, confirmability of findings will be assessed using audit and feedback and fidelity checks to determine how the workflows are implemented or modified as the dyads are onboarded [47].

An indicator on the OASIS diagnosis list documenting the identification of sepsis survivors at the beginning of HHC will be modeled using hierarchical logistic regression. We will use Medicare claims dates and site of service to identify the timing of HHC nursing visits and community provider visits. This indicator for whether the protocol for timely nursing and community provider visits was achieved will be modeled using hierarchical logistic regression. At the 12-month point from the go-live start of implementation, the study team will stop communicating and monitoring fidelity with the stakeholders. Outcomes of sepsis diagnoses and visit patterns will be compared during the “maintenance” period evaluating for stability or decline in the proportion of sepsis survivors identified and/or receiving the early visits compared to the intervention period. Hierarchical regressions will be extended through the maintenance period and separate treatment indicators for the intervention period and the maintenance period. Regressions will test equality of coefficients on the treatment indicators on the two periods. Equality of coefficients will imply maintenance of effects after the study team exits. A data monitoring committee is unnecessary as this is a low-risk, implementation science study with voluntary partners.

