Our I-TRANSFER intervention is designed to address several barriers and gaps that may jeopardize the implementation of early post-acute surveillance. Sepsis survivors are not consistently identified with a medical diagnosis of sepsis until after discharge from acute care [51–55]. This results in the diagnosis and other patient characteristics not being adequately communicated to the next level of care [1, 39, 40, 56]. Home health clinicians likely do not know they are receiving a sepsis survivor. Second, there is little evidence to guide the transition of sepsis survivors to HHC. Our protocol is designed to provide a critically needed, especially post-pandemic, best practice intervention model to clinicians and the HHC industry nationwide. This protocol is even more timely given the pandemic, as research suggests that COVID-19 can lead to sepsis [57] and many hospitalized patients prefer to recover at home due to skilled nursing facility capacity and safety concerns [58]. Third, among sepsis survivors transitioned to HHC, and not readmitted within the first week, only 28% received the early visit protocol, shown by our team to be associated with significantly reduced readmissions [24]. This presents an important opportunity to generate further evidence of effectiveness and inform widespread implementation to help many more sepsis survivors. Our advisory group, comprised of national leaders in sepsis care and HHC professional organizations will facilitate widespread dissemination of our findings, from academic nursing and medicine to industry practitioners.

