#### Aim 2, I-TRANSFER implementation

Aim 2 of our study is to produce insights and generalizable knowledge regarding the context, processes, strategies, and determinants of I-TRANSFER implementation. We will assess readiness of the sites using the Organizational Readiness for Implementing Change (ORIC) survey. The ORIC survey includes 12 questions related to the participant’s perception of their organization’s readiness to implement the intervention including characteristics like confidence, motivation, support, flexibility, addressing challenges, and coordination [59]. We will study the implementation using qualitative methods guided by the Consolidated Framework for Implementation Research (CFIR) [60]. We will also test two process hypotheses. First, compared to usual care, sepsis survivors receiving I-TRANSFER will have sepsis identified as a HHC diagnosis on the Outcomes Assessment Information Set (OASIS) significantly more often. Second, sepsis survivors receiving I-TRANSFER will receive early and intense HHC nursing visits (within 2 days of hospital discharge + 1 more that week) and community provider visits by 7-days more often. The OASIS is a comprehensive assessment tool, mandated by the Centers for Medicare and Medicaid (CMS), designed to collect nearly 100 items related to a home health recipient’s functional status, clinical status, and service needs at several time points during a HHC episode [34].

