### Study period

Onboarding is a 6-month period when the implementation and research teams plan the implementation. Intervention is the 12-month period when I-TRANSFER is in operation. Maintenance is a 6-month period when the research team assesses whether the intervention continues without research team monitoring and feedback. The analysis will be an intent to treat. We will adjust for time, or any health system interventions, as well as patient covariates that may confound the findings using generalized mixed models.

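### The maintenance rule treats a failure to reject equal coefficients as sustained effect, so a real partial decline in the Aim 2 process outcomes could be reported as maintained

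*Protocol article*

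**What the plan says.** Under Analysis, Aim 2, the article models two binary process outcomes by hierarchical logistic regression: sepsis on the OASIS diagnosis list, and receipt of the early nursing and provider visits. The models are then extended through the maintenance period, with a separate treatment indicator for each period. The aim is given as "evaluating for stability or decline in the proportion of sepsis survivors identified and/or receiving the early visits compared to the intervention period". The test is "Regressions will test equality of coefficients on the treatment indicators on the two periods", and its reading is "Equality of coefficients will imply maintenance of effects after the study team exits". The passage gives no size of decline that would matter, and it does not require that an intervention effect be shown first.

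Study period fixes the two lengths: "Intervention is the 12-month period when I-TRANSFER is in operation" and "Maintenance is a 6-month period when the research team assesses whether the intervention continues without research team monitoring and feedback".

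Study aims and hypothesis, Aim 2, separately compares both process outcomes with usual care: "compared to usual care, sepsis survivors receiving I-TRANSFER will have sepsis identified as a HHC diagnosis", and "sepsis survivors receiving I-TRANSFER will receive early and intense HHC nursing visits" along with timely provider visits more often.

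**The concern.** A test of equality can reject equality or fail to reject it; it cannot establish it. A rule that reads equality as maintenance therefore works, in use, as a rule that reads non-rejection as maintenance. This puts the burden of proof the wrong way round: fewer records, more variation between dyads over time, or noisier coding all make the favourable answer easier to reach. The maintenance period is half as long as the intervention period and covers the same five dyads, so the contrast is not rich in information.

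What is at stake is whether the OASIS diagnosis and the early visits hold up without research-team monitoring and feedback. A partial fall is a plausible pattern once monitoring stops, and it is the pattern that this rule is least able to tell from stability. A mistaken claim of durability would suggest to agencies that continued monitoring is not needed.

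A lesser gap is that the rule is not tied to a demonstrated intervention effect, so two coefficients near zero also satisfy it.

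**Working it through.** The article gives no sample size or power for this comparison, so there is no stated figure to reproduce. Its only such figures (Study sample, Aim 1) concern readmission. The following is an illustration.

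**Inputs from the article**
- Usual-care receipt of the early visits: 28% (Background: "only 28% received the early visit protocol", among survivors not readmitted in the first week).
- Site volume: 869 per period (Study sample, Aim 1). The length of that period is not stated.
- Intervention 12 months, maintenance 6 months, five dyads.

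**Assumptions**
- 869 records in the intervention period. For maintenance, 869 × 6/12 ≈ 435 if a period means 12 months, or 869 if the figure applies to both periods.
- Intervention-period receipt of 38%, 50% or 60%.
- Half of the gain over 28% is lost in maintenance.
- Two-sided 5% test.
- Design effect D of 1 (no clustering), 2 or 3.
- Difference in proportions, as an approximation to the logistic contrast.

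**Formulas**
- SE = √{D × [p₁(1−p₁)/n₁ + p₂(1−p₂)/n₂]}
- z = |p₁ − p₂| / SE
- Probability of not rejecting = 1 − [Φ(z − 1.96) + Φ(−z − 1.96)]

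**Worked case, 38% to 33%, 869 against 435, D = 1**
- SE = √(0.38×0.62/869 + 0.33×0.67/435) = 0.0279
- z = 0.05/0.0279 = 1.79
- Probability of not rejecting = 57%

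**Probability that loss of half the gain is not detected**

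| Decline | Records | D = 1 | D = 2 | D = 3 |
|---|---|---|---|---|
| 38% to 33% | 869 / 435 | 57% | 76% | 82% |
| 38% to 33% | 869 / 869 | 41% | 66% | 76% |
| 50% to 39% | 869 / 435 | 3% | 23% | 41% |
| 60% to 44% | 869 / 435 | 0% | 3% | 11% |

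The first two rows show the reversed incentive. The decline is the same, but halving the maintenance records raises the chance of reading it as maintained from 41% to 57% without clustering.

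**No effect in either period (28% and 28%).** The test does not reject 95% of the time. This is true by construction for any 5% test of a true null.

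**The case against.** Several points on the other side are sound, and they limit the finding.

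- **The text does not mention significance or proof.** It also says that stability or decline in the proportions will be evaluated, so the estimated change will be seen. This stands as a point about wording. But the article names a test and then attaches a conclusion to equality, and non-rejection is the only outcome of that test that could be taken as equality.
- **Large losses would usually be found.** A reader might infer that any real decline would go unnoticed. The figures do not support that: loss of half of a gain to 60% is missed at most 11% of the time here. The weakness is with modest gains and partial declines.
- **An ineffective intervention would not pass unnoticed.** A reader might infer that no effect at all would be reported as sustained benefit. Both process outcomes are tested against usual care, and the same model shows the intervention-period coefficient, so a null effect would be visible. What remains is that the maintenance rule is not made conditional on that result.
- **The inputs are assumed.** Both periods come from the same dyads, so stable differences between dyads largely cancel. Only variation within dyads over time inflates the contrast, and design effects of 2 to 3 may be too high. This is why the unclustered and equal-period figures are shown; the modest-gain miss rate is still 41% at best.
- **A numeric margin may be left to the analysis plan.** Agreed; its absence is not the point. The point is an inference rule that the article does state, and states wrongly.
- **This is not a main conclusion of the study.** The abstract does not mention maintenance, and the primary outcome and its analysis are untouched.

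**Conclusion.** The point holds at moderate severity and for the Aim 2 maintenance comparison only. As written, the rule takes non-rejection of equality as evidence of maintenance, so a real partial decline in OASIS sepsis identification or early visits could be reported as maintained.

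The size depends mainly on how large the intervention-period gain turns out to be. For a 10-point gain half lost, the miss rate runs from 41% (equal periods, no clustering) to 82% (435 maintenance records, design effect 3). For a 32-point gain half lost, it is 0% to 11%. These figures rest on the assumed period sizes, uptake rates and design effects. They start from the 28% visit rate and so illustrate the visit outcome rather than the OASIS diagnosis. The logical fault in the rule does not depend on any of them.

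**What to change.** Replace the sentence that equates equality with maintenance by a rule with these parts:

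1. Claim maintenance of a process outcome only if its intervention-period effect against usual care has been shown.
2. Require also that the confidence interval for maintenance minus intervention excludes a decline larger than a margin fixed before the maintenance outcomes are analysed. Loss of half the intervention-period gain is one possible margin; the choice belongs to the investigators.
3. Report the change, or the fraction of the gain retained, with its interval.
4. Call a non-significant equality test on its own inconclusive.

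The cost is a few sentences and one margin, with the same models and data. The real downside is that the result may be inconclusive more often. With the half-the-gain margin m, no true decline, one-sided 2.5% and 80% power, equal periods need n = (1.960 + 0.842)² × 2p(1−p)/m² records each, before clustering:

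- p = 38%, m = 5 points: 7.85 × 2 × 0.2356/0.0025 ≈ 1,480 per period, or 2,220 + 1,110 with a half-size maintenance period.
- p = 50%, m = 11 points: 7.85 × 2 × 0.25/0.0121 ≈ 325 per period, or 487 + 244.

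On the assumed 869 and 435 records, a maintenance claim is within reach for a large gain and probably not for a modest one. It is better to state that in advance than to let the equality test conceal it.
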